## Abstract

**Background::**

When safe to do so, avoiding blood transfusions in cardiac surgery can avoid the risk of transfusion-related infections and other complications while protecting a scarce resource and reducing costs. This protocol describes a kidney substudy of the Transfusion Requirements in Cardiac Surgery III (TRICS-III) trial, a multinational noninferiority randomized controlled trial to determine whether the risk of major clinical outcomes in patients undergoing planned cardiac surgery with cardiopulmonary bypass is no greater with a restrictive versus liberal approach to red blood cell transfusion.

**Objective::**

The objective of this substudy is to determine whether the risk of acute kidney injury is no greater with a restrictive versus liberal approach to red blood cell transfusion, and whether this holds true in patients with and without preexisting chronic kidney disease.

**Design and Setting::**

Multinational noninferiority randomized controlled trial conducted in 73 centers in 19 countries (2014-2017).

**Patients::**

Patients (~4800) undergoing planned cardiac surgery with cardiopulmonary bypass.

**Measurements::**

The primary outcome of this substudy is perioperative acute kidney injury, defined as an acute rise in serum creatinine from the preoperative value (obtained in the 30-day period before surgery), where an acute rise is defined as ≥26.5 μmol/L in the first 48 hours after surgery or ≥50% in the first 7 days after surgery.

**Methods::**

We will report the absolute risk difference in acute kidney injury and the 95% confidence interval. We will repeat the primary analysis using alternative definitions of acute kidney injury, including staging definitions, and will examine effect modification by preexisting chronic kidney disease (defined as a preoperative estimated glomerular filtration rate [eGFR] <60 mL/min/1.73 m^2^).

**Limitations::**

It is not possible to blind patients or providers to the intervention; however, objective measures will be used to assess outcomes, and outcome assessors will be blinded to the intervention assignment.

**Results::**

Substudy results will be reported by the year 2018.

**Conclusions::**

This substudy will provide generalizable estimates of the risk of acute kidney injury of a restrictive versus liberal approach to red blood cell transfusion in the presence of anemia during cardiac surgery done with cardiopulmonary bypass.

**Trial Registration::**

www.clinicaltrials.gov; clinical trial registration number NCT 02042898.

## What was known before

Initiating transfusions at a lower level of hemoglobin substantially reduces the number of transfusions performed with no adverse impact on clinical outcomes; however, uncertainty remains in the setting of cardiac surgery where patients may have less ability to tolerate anemia.

## What this adds

This substudy of Transfusion Requirements in Cardiac Surgery III (TRICS-III), a multinational noninferiority randomized controlled trial, will provide new knowledge on the risk of acute kidney injury of a restrictive versus liberal approach to red blood cell transfusion in the presence of anemia during cardiac surgery done with cardiopulmonary bypass.

## Introduction

Almost 20 million cardiac surgeries are performed worldwide each year, and the period during and shortly after cardiac surgery consumes 15% to 20% of the red blood cell supply available for transfusion.^1,2^ When safe to do so, avoiding blood transfusion in this setting protects a scarce resource, reduces costs, and avoids the risk of transfusion-related infection and other complications, which can include myocardial infarction, stroke, and acute kidney injury.^3,4^ However, the risks of transfusion must be balanced against the risks of untreated anemia, which can compromise tissue oxygenation and also increase the risk of myocardial infarction, stroke, and acute kidney injury.^5^

Avoiding unnecessary red blood cell transfusions in cardiac surgery has been identified as a critical area for research.^2^ Emerging evidence suggests that initiating transfusions at a lower level of hemoglobin substantially reduces the number of transfusions performed with no adverse impact on clinical outcomes.^4,6^ These data come from randomized controlled trials as it is impossible to reliably disentangle the adverse effects of anemia and red blood cell transfusion in observational studies. In controlled trials, patients were randomized to receive a restrictive versus liberal approach to transfusion initiation, where initiation occurred at a lower versus higher level of hemoglobin, typically 75 g/L versus 95 g/L, respectively.^4,6^ Meta-analyses of trials examining these approaches have been done in the nonsurgical and surgical setting, including small trials of patients undergoing cardiac surgery. While these studies suggest that a restrictive versus liberal approach to red blood cell transfusion is safe,^4,6-9^ uncertainty remains in the setting of cardiac surgery where patients may have less ability to tolerate anemia, and where trials conducted to date have been too small to determine whether there are meaningful differences in outcomes between the 2 groups.^4,6,8,10^

Prompted by the need for better evidence, the Canadian, Australian, and New Zealand governments provided funding for a noninferiority multicenter randomized controlled trial to test the hypothesis that the risk of adverse clinical outcomes from cardiac surgery with cardiopulmonary bypass is no greater with a restrictive versus liberal approach to red blood cell transfusion. The Transfusion Requirements in Cardiac Surgery III (TRICS-III) trial (NCT02042898) was launched in 2013 and includes over 4800 patients. The primary outcome of adverse events from cardiac surgery is a composite of all-cause mortality, myocardial infarction, new focal neurological deficit, and new kidney failure treated with dialysis, as assessed within 28 days of surgery or at hospital discharge, whichever comes first.

Approximately 1% of patients who undergo cardiac surgery will develop severe acute kidney injury and receive dialysis in the perioperative period. Many more patients (over 15%) will develop an important degree of acute kidney injury^11-13^ that is not treated with dialysis but is still associated with short- and long-term mortality, a longer hospital stay, and higher health care costs.^11,14-17^ This evidence prompted us to develop a kidney substudy of the TRICS-III trial. Our substudy will test the hypothesis that the risk of perioperative acute kidney injury is no greater with a restrictive approach to red blood cell transfusion during cardiac surgery than a liberal approach. We also want to know whether this holds true in patients with and without preexisting chronic kidney disease. This protocol describes our plan to conduct these kidney substudy analyses in TRICS-III.

### Primary Question

Among patients undergoing planned cardiac surgery with cardiopulmonary bypass, is a restrictive approach to red blood cell transfusion noninferior to a liberal approach with respect to the risk of perioperative acute kidney injury?

### Secondary Question

2. Does the presence of preexisting chronic kidney disease modify the effect of a restrictive versus liberal approach to transfusion with respect to the risk of acute kidney injury?

## Methods

### The TRICS-III Trial

TRICS-III (NCT02042898) is a multinational, open-label randomized controlled trial testing 2 commonly used red blood cell transfusion approaches in high-risk patients undergoing planned cardiac surgery with cardiopulmonary bypass (recruitment period 2014 to 2017; funded by the Canadian Institutes of Health Research, the National Health and Medical Research Council of Australia, and the Health Research Council of New Zealand). The prespecified methods of this large international trial are described elsewhere (available from the authors upon request).^18^ Briefly, this parallel group, pragmatic, noninferiority trial was designed to evaluate whether a restrictive approach to transfusion is no worse than a liberal approach with respect to a composite primary outcome of all-cause mortality, myocardial infarction, new focal neurological deficit, and new kidney failure treated with dialysis. The primary outcome will be assessed up to postoperative day 28 or at hospital discharge, whichever comes first. Planned enrollment was 5000 patients, and the trial accrual ended in March 2017 with 5028 randomized patients across 73 centers in 19 countries (as described below, 4850 randomized participants completed surgery). The data are currently being prepared for analysis (no between-group outcome analyses have yet taken place).

#### Randomization and intervention

Patients were identified in the preoperative anesthesia or cardiac surgery clinic or in the in-patient unit at each hospital, where informed consent was obtained. Enrolled patients were randomized to receive a restrictive or liberal approach to red blood cell transfusion. Randomization was generated centrally online by the Applied Health Research Centre at the Li Ka Shing Knowledge Institute of St. Michael’s Hospital (Toronto, Ontario, Canada). Randomization was stratified by center using random permuted blocks of varying sizes. For the restrictive approach, transfusion was not initiated until a patient’s hemoglobin concentration fell below 75 g/L intraoperatively and/or postoperatively in the intensive care unit or on the hospital ward. For the liberal approach, transfusion was initiated once a patient’s hemoglobin concentration fell below 95 g/L intraoperatively or postoperatively in the intensive care unit or if it fell below 85 g/L on the ward. For each group, transfusion occurred within the following time frames of the hemoglobin trigger: within 2 hours for patients in the operating room, within 18 hours for patients in the intensive care unit, and within 40 hours for patients on the hospital ward.

### Methods Used in the TRICS-III Kidney Substudy

Ethics approval was obtained for additional renal data collection at all 73 participating centers (in 19 countries). Key aspects of the TRICS-III protocol that are relevant to the proposed kidney substudy are described below.

### Patient Selection

Inclusion criteria for the TRICS-III main trial were as follows: adults aged 18 years or older undergoing a planned cardiac surgery with cardiopulmonary bypass, and a Preoperative European System for Cardiac Operative Risk Evaluation (EuroSCORE I) of 6 or more. Exclusion criteria were patient refusal or inability to receive blood products, involvement in the autologous predonation program, having a heart transplant, having a type of surgery solely for an insertion of a ventricular assist device, and the presence of pregnancy or lactation. Patients who were randomized but who did not undergo cardiac surgery will be excluded from the analysis (we expect ~3% of randomized patients did not undergo surgery).

The following additional exclusions will be applied to the TRICS-III kidney substudy:

Patients with preoperative end-stage kidney disease, defined as previous chronic dialysis, receipt of a kidney transplant, or an estimated glomerular filtration rate (eGFR) <15 mL/min per 1.73 m^2^ (these patients will be excluded because the prevention of postoperative acute kidney injury is no longer relevant; we expect <2% of randomized patients to be excluded for this reason^19^).Patients missing a preoperative serum creatinine value (because preoperative serum creatinine is necessary to identify acute kidney injury, which is defined by an acute increase in serum creatinine from the preoperative value; we expect <1% of randomized patients will be missing a preoperative serum creatinine value).Patients having *emergency* cardiac surgery will be excluded for 2 reasons: (1) They frequently have acute kidney injury or other complications prior to surgery, and so the preoperative serum creatinine may not be stable at baseline and (2) unfortunately many die, either in the operating room or shortly thereafter, before postoperative acute kidney injury develops (we expect <1% of randomized patients will have undergone emergency cardiac surgery).

### Data Collection and Outcomes

Preoperative serum creatinine was obtained within the 30-day period before surgery, where the most recent value before surgery will serve as the baseline value. Participating sites received study funds to measure the postoperative serum creatinine on days 1, 2, 3, and 5 after surgery. To our knowledge, at participating sites, serum creatinine measurements were traceable to isotope dilution mass spectrometry. No urine output data will be used in the primary analysis of this substudy given difficulties with accurately measuring this variable outside of the intensive care unit.

The primary outcome of the TRICS-III kidney substudy is perioperative acute kidney injury, defined as an acute rise in serum creatinine from the preoperative baseline value, where an acute rise is defined as ≥26.5 μmol/L in the first 48 hours after surgery or ≥50% in the first 7 days after surgery.^20^ Results from an earlier cardiac study with similar enrollment criteria as TRICS-III suggests that our data collection schedule will capture most perioperative acute kidney injury events in the first 5 days of surgery; in this previously published prospective surgery study of 1219 cardiac patients, 15% of patients developed perioperative acute kidney injury (as per our definition); 13.9% of events were observed in the hours following surgery and 38.7%, 38.7%, and 8.7% of events were observed on postoperative days 1, 2 and 3, respectively.^21^ For this reason, our protocol provides each center funding for serum creatinine measures on days 1, 2, 3, and 5 to encourage measurement on these days in all patients; as well, any other serum creatinine measures obtained in the perioperative period as part of routine care are recorded in the trial database (recording both their value and their date). We will compare the number of serum creatinine measurements (and the postoperative days of these measurements) in each intervention group during the hospital stay to examine the potential for ascertainment bias. While health care providers in TRICS-III are aware of the intervention received, this was also the case in our analyses of acute kidney injury within a large randomized trial where coronary artery bypass surgery was done with and without a bypass pump (where there was no difference in the frequency of serum creatinine measurement between the 2 groups given how ubiquitous serum creatinine measurements are in routine care in the perioperative setting^19^). We expect that less than 2% of patients will be missing serum creatinine values in the first 2 days of surgery as a result of death.

### Statistical Power

The TRICS-III study is designed to test whether a restrictive approach to transfusion is noninferior to a liberal approach. The total required sample size for the TRICS-III kidney substudy is 3378 based on a noninferiority margin of 3.5% for an absolute risk increase in acute kidney injury with the restrictive versus liberal approach, a 1-sided alpha of 0.025, and 85% power, assuming a baseline rate of acute kidney injury of 15%, <2% missing data due to death, and ~85% meeting our eligibility criteria. Thus, our projected available sample size of 4074 patients for this substudy will be adequate. A noninferiority margin of 3.5% is a reasonable minimal clinically important difference; for example, in our prior analyses of acute kidney injury within a large randomized trial, coronary artery bypass surgery done without a bypass pump reduced the relative risk of acute kidney injury by 17% (95% confidence interval, 3%-28%) compared with surgery done with a bypass pump, but without evidence of better preserved kidney function, mortality, or any other relevant clinical outcome 1 year later (with a baseline rate of 15%, a relative risk increase of 17% represents an absolute risk increase of about 2.5%).^19^

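### The stated requirement of 3378 patients does not follow from its own inputs, which give 3738; the projected 4074 is still adequate, but with half the apparent reserve

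*Protocol article*

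**What the plan says.** The Statistical Power section of the protocol article gives the required number and its drivers in one sentence. It reads "The total required sample size for the TRICS-III kidney substudy is 3378 based on a noninferiority margin of 3.5" (per cent), then "a 1-sided alpha of 0.025, and 85% power, assuming a baseline rate of acute kidney injury of 15" (per cent). The same sentence names two allowances: under 2% missing because of death, and roughly 85% of patients eligible. The next sentence concludes that "our projected available sample size of 4074 patients for this substudy will be adequate".

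The Statistical Analysis section fixes the matching test: a large-sample normal 95% confidence interval for the difference in proportions (restrictive minus liberal), with noninferiority accepted if its upper limit is below 3.5%. It makes the per-protocol analysis primary and expects about 10% of randomized participants to be excluded from it.

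**The concern.** A noninferiority sample size for two proportions is fully determined by the event rate, margin, alpha, power, allocation ratio and assumed true difference. The article states the first four. With conventional values for the last two, the result is 360 patients above the printed figure. The allowances for death and eligibility cannot close the gap, because they can only raise a requirement.

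The printed figure is the only benchmark against which the projected sample is called adequate. If it is about 10% too low, the margin of safety looks roughly twice as large as it is, and the wrong number may be carried into the report of results.

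**Working it through.** **Inputs from Statistical Power:** event rate 0.15; margin 0.035; one-sided alpha 0.025 (z = 1.95996); power 85% (z = 1.03643); stated requirement 3378; projected sample 4074.

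**Input from Statistical Analysis:** normal-approximation interval for a risk difference, hence the unpooled variance.

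**Assumptions not stated in the article:** 1:1 allocation, taken from the two-group parallel design, and a true difference of zero, so 15% in both arms.

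**Step 1. Try to reproduce 3378.**

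n per arm = 2 × 0.15 × 0.85 × (1.95996 + 1.03643)² / 0.035² = 1868.97, rounded up to 1869. The total is 2 × 1869 = 3738.

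The printed figure is not reproduced. It is 3738 − 3378 = 360 below, and 360 / 3738 = 9.6%.

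**Step 2. Add the stated allowance for death.** 3738 / 0.98 = 3814.3, so 3815. Dividing by 0.85 for eligibility as well gives about 4488. Both move away from 3378.

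**Step 3. Look for another route to 3378.**

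| Calculation | Total |
|---|---|
| Restricted-variance (Farrington-Manning) | 3756 |
| Continuity-corrected | 3852 |
| Variance at 15% vs 18.5% | 4080 |
| 80% power instead of 85% | 3268 (about 3335 after 2% loss) |
| Superiority test, 15% vs 11.5% | 3362 to 3370 |

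The first three keep the stated inputs and give larger numbers. The fourth contradicts the stated power. The fifth tests a different hypothesis in the opposite direction. None gives 3378.

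To obtain about 3378 at 85% power, one input would have to change without being stated: a common event rate of about 13.3%, a margin of about 3.7%, or a true benefit of about 0.2 percentage points with restrictive transfusion.

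**Step 4. Power at the relevant sizes.** Power(N) = Φ(0.035 / √(0.255 / (N/2)) − 1.95996), where 0.255 = 2 × 0.15 × 0.85.

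| Evaluable patients | Power |
|---|---|
| 3378 | 81.3% |
| 3738 | 85.0% |
| 4074 | 87.9% |
| 4074 × 0.98 ≈ 3993 | 87.2% |
| 4074 × 0.90 ≈ 3667 | 84.3% |

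Simulation of the planned confidence-interval rule gave 81.3% at 3378 and 85.0% at 3738.

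**Step 5. The reserve.** As printed: 4074 − 3378 = 696. Corrected: 4074 − 3738 = 336. Against 3815 it is 4074 − 3815 = 259.

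**Step 6. What 4074 may contain.** Patient Selection expects under 2% with end-stage kidney disease, under 1% without a preoperative creatinine and under 1% with emergency surgery. Statistical Power adds under 2% for death, and Statistical Analysis 10% for per-protocol exclusions. At their upper limits these sum to 2 + 1 + 1 + 2 + 10 = 16%. The 4850 patients who completed surgery (section on the TRICS-III trial) × 0.84 = 4074 exactly. This suggests that the per-protocol exclusions are already taken out, but the article does not show the derivation.

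**The case against.** The strongest reply is that nothing in the trial turns on 3378. The figure is used once, to call 4074 adequate, and 4074 exceeds the corrected requirement with or without the allowance for death. Accrual had ended, so 3378 set no recruitment target. The margin, the estimator and the decision rule do not depend on it. All of this stands, and it limits the severity.

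A second reply is that the article does not state the true difference or the allocation ratio, and a small assumed benefit would bring the requirement down to 3378. This also stands in part: the correction must leave room for the sponsor to state such an assumption. Nothing in the article suggests that one was made.

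Three stronger readings are tempting but not supported:

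- A reader might infer that the substudy is underpowered. It is not on its own projection: power at 4074 is above the stated 85%.
- A reader might take 3378 as a count before the death and eligibility allowances, leaving about 2814 evaluable (3378 × 0.98 × 0.85) and 73.9% power. The article compares 3378 directly with patients available for the substudy, so this would apply the eligibility allowance a second time.
- A reader might fear that a per-protocol set between 3378 and 3738 would be passed as adequate. The article contains no rule that checks the achieved number against 3378; noninferiority is judged by the confidence limit alone.

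**Conclusion.** The required sample size is wrong as written. On the article's inputs, with 1:1 allocation and no true difference, it is 3738 evaluable patients, or about 3815 with 2% lost to death. The printed figure would deliver about 81% power instead of 85%.

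The adequacy statement holds, with about 88% power at 4074, but the reserve is 336 patients, not 696. One uncertainty remains: if 4074 does not already exclude the anticipated 10%, the primary per-protocol analysis would have about 84% power, slightly under the stated 85%. The match with 4850 × 0.84 points the other way without proving it.

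The two middle digits of 3738, when swapped, give 3378, so a transcription slip is the likely cause; the article cannot confirm this. Severity is moderate: a headline design figure is off by about 10% in the favourable direction, with no change to the conduct or the decision rule.

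**What to change.** In Statistical Power:

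- Replace 3378 with 3738 evaluable patients (about 3815 allowing for 2% lost to death), and name the assumptions of 1:1 allocation and no true difference. Alternatively, keep 3378 and state the assumption that yields it.
- Report that the projected 4074 gives about 88% power at a 15% event rate, or about 87% if a further 2% are lost.
- Show how 4074 was obtained, and say whether the 10% per-protocol exclusions are already removed. If they are not, report about 84% power for the primary analysis.

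The cost is a few lines of text. No new patients and no change to the margin or analysis are needed; the stated reserve simply becomes less generous.

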### Statistical Analysis

As recommended, we will conduct both per-protocol and intention-to-treat analyses^22,23^; however, the per-protocol analysis will be considered primary. We will report the stability of the noninferiority conclusion between the per-protocol and intention-to-treat results,^22,23^ and congruence in results between these analyses will increase confidence in our interpretation of the findings. Per-protocol analyses are often preferred for addressing questions of noninferiority because compared with intention-to-treat analyses they reduce the risk of falsely declaring noninferiority when a meaningful difference between the effects of 2 interventions in truth exists. In contrast, intention-to-treat analyses are preferred for questions of superiority because they reduce the risk of falsely declaring superiority when the effects of the interventions are, in truth, similar. As outlined in the TRICS-III main protocol, the per-protocol analyses will exclude (1) patients whose adherence to the assigned transfusion strategy is less than 90% and/or (2) patients who withdraw from the study at any time (including withdrawal of the patient by their treating physician). Currently, we anticipate an estimated 10% of randomized participants will be excluded from the per-protocol analysis; this subgroup of patients will be examined carefully to assess the potential for bias in the per-protocol analysis. In the intention-to-treat analyses (described below), all participants will be analyzed according to their original randomized group assignment regardless of whether transfusion occurred or which transfusion approach was followed. We will report the unadjusted absolute risk difference between the 2 groups with a 95% confidence interval using the large-sample normal approximation for a difference in proportions. We will accept noninferiority if the upper limit of the 2-sided 95% confidence interval for the difference in proportions of acute kidney injury (proportion of acute kidney injury in the restrictive-approach group minus the proportion in the liberal-approach group) is less than the noninferiority margin of 3.5%. We expect that data on postoperative serum creatinine will be missing for <2% of participants due to death and <5% due to missing data. For patients who were randomized but are missing at least 1 postoperative serum creatinine value, we will use recommended model-based multiple imputation methods using all available data to impute acute kidney injury status.^24-26^

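### The assumed 85% eligibility conflicts with listed exclusions of under 4%, and the sample-size assumptions do not name the 10% per-protocol loss

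*Protocol article*

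**What the plan says.** The Statistical Power section of the protocol article gives a required total of 3378, based on a "noninferiority margin of 3.5% for an absolute risk increase in acute kidney injury", "a 1-sided alpha of 0.025, and 85% power", and "assuming a baseline rate of acute kidney injury of 15%, <2% missing data due to death, and ~85% meeting our eligibility criteria". It then concludes that "our projected available sample size of 4074 patients for this substudy will be adequate".

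The Patient Selection section gives three substudy exclusions with expected sizes:
- preoperative end-stage kidney disease ("we expect <2% of randomized patients to be excluded for this reason");
- no preoperative creatinine (under 1%);
- emergency surgery ("we expect <1% of randomized patients will have undergone emergency cardiac surgery").

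Separately, it expects about 3% of randomized patients not to have had surgery. The section on the TRICS-III trial reports 5028 randomized, of whom 4850 completed surgery.

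The Statistical Analysis section makes the per-protocol analysis primary and states that "we anticipate an estimated 10% of randomized participants will be excluded from the per-protocol analysis". Per-protocol exclusion is for adherence below 90% or for withdrawal. The same section plans multiple imputation where postoperative creatinine is missing.

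**The concern.** Two statements about the same population disagree. The listed exclusions leave about 96% of operated patients, or about 93% of randomized patients once those without surgery are also removed. Neither is 85%. The exclusion figures are upper bounds, so the true gap could only be wider.

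The largest expected loss from the primary analysis set is the 10% per-protocol exclusion, and it is absent from the list of sample-size assumptions. Poor adherence and withdrawal occur after randomization, so they are not eligibility criteria in the ordinary sense.

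A reader therefore cannot tell whether 4074 is the number before or after the per-protocol loss. That decides which analysis set the adequacy statement covers and how much power the primary analysis has.

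**Working it through.** **Inputs.** Event rate 15%, margin 3.5%, one-sided alpha 0.025, power 85%, death loss under 2%, eligibility about 85%, available sample 4074 (Statistical Power); exclusions of under 2%, 1% and 1% (Patient Selection); 4850 operated and 5028 randomized (The TRICS-III Trial); per-protocol loss 10% (Statistical Analysis). Assumed here: 1:1 allocation and the same 15% rate in both arms.

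**Step 1. Reproduce 4074 from the factors as labelled.**
- 4850 × 0.85 = 4123
- 4850 × 0.85 × 0.98 = 4040

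Both are close to 4074 (within about 1.2%), but neither equals it.

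**Step 2. Reproduce 4074 from the itemised losses.**
- Additive: 1 − (0.02 + 0.01 + 0.01 + 0.02 + 0.10) = 0.84, and 4850 × 0.84 = 4074, an exact match.
- Multiplicative: 0.98 × 0.99 × 0.99 × 0.90 × 0.98 = 0.847, which rounds to the stated 85%. With the exclusions rounded to 4%, 4850 × 0.96 × 0.90 × 0.98 = 4107.

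Either way, the 85% is recovered only if the 10% per-protocol loss is included. The listed exclusions alone give 0.98 × 0.99 × 0.99 = 0.960.

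**Step 3. Required size from the stated inputs.**
n per arm = 2 × 0.15 × 0.85 × (1.960 + 1.036)² / 0.035² = 1869, so 3738 in total. The printed 3378 does not reproduce. At that size power is 81.3%.

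**Step 4. Power under each reading.**
Power = Φ(0.035/SE − 1.960), with SE = √(4 × 0.15 × 0.85 / N).

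| Reading | Set | N | Power |
|---|---|---|---|
| 10% already inside 4074 | per-protocol | 4074 | 87.9% |
| Same losses, multiplied | per-protocol | 4107 | 88.1% |
| Literal: 10% comes off 4074 (× 0.90) | per-protocol | 3667 | 84.3% |
| Literal: 10% comes off 4040 (× 0.90) | per-protocol | 3636 | 84.0% |
| 4850 × 0.96, deaths imputed | intention-to-treat | 4656 | 91.7% |
| 4850 × 0.96 × 0.98, deaths removed | intention-to-treat | 4563 | 91.2% |

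**The case against.** The strongest reply is that nothing of substance is wrong. The 85% is marked approximate, and the product of all the losses is 0.847. Applied to the roughly 4800 patients of the abstract, 85% gives 4080; applied to 4850 it gives 4123. On that view 4074 is a sound per-protocol figure with loose wording around it. Most of this stands: 4074 can be derived from the article's own numbers, and a reader who inferred that it has no basis would be wrong.

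A reader might also infer that the primary analysis is underpowered. The documents do not support that. The shortfall needs two things together: the 10% taken off 4074 a second time, and the recomputed 3738 as the benchmark. Against the printed 3378, both 3667 and 3636 suffice. Even then the deficit is 0.7 to 1.0 percentage points.

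The reconstruction itself can be challenged. The article states the exclusion and per-protocol percentages as shares of randomized patients, whereas the exact match applies them to operated patients. Taking 16% of 5028 (about 804) from 4850 gives about 4046, not 4074. The match is good evidence of what was done but not proof.

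Finally, an article may leave a full patient-flow derivation to the longer protocol. That is fair, and the absence of one is not the complaint. The complaint is that two printed figures disagree and that a loss is carried under the wrong label.

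**Conclusion.** The point holds as a labelling error in the planning assumptions. An eligibility share of about 85% contradicts listed exclusions of under 4%, and the 10% loss that defines the primary set is not named where the sample size is justified. The likeliest explanation is that the 10% was counted inside the 85%. In that case 4074 is the per-protocol size, power is about 88%, and 4074 exceeds both the printed 3378 and the recomputed 3738, so the conclusion of adequacy stands. Only the literal reading gives about 3667 and 84.3%, marginally below target. The intention-to-treat set is larger on the listed exclusions and carries no power risk.

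These figures rest on 1:1 allocation, a 15% rate in both arms, the listed upper bounds taken at face value, and 4850 as the base. The failure of 3378 to reproduce is a separate and numerically larger error.

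**What to change.** In Statistical Power, replace the 85% eligibility assumption with the itemised losses and their base: 4850 operated, about 96% eligible, about 10% per-protocol exclusion, and under 2% for death if deaths are removed rather than imputed. Say whether each percentage refers to randomized or operated patients. Once the authors confirm it, state that 4074 is the per-protocol set.

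Give the intention-to-treat size as well: about 4560 if deaths are removed, or about 4656 if they are imputed (power about 91% to 92%). The choice should agree with the imputation plan in Statistical Analysis and with the intention-to-treat section, which analyses all participants.

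In the same sentence, correct 3378 to 3738 or state the inputs that produce 3378.

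The cost is wording only. Accrual has ended, the article says no between-group outcome analysis has taken place, and neither the design nor the analysis changes.
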